BrainFx is a for-profit firm that creates proprietary neurological assessment software designed to identify signs of brain function impairment. The BrainFx Screen (SCREEN) is an unvalidated, digitally administered, 15-minute, 7-question screen designed to identify early signs of MCI by assessing functional deficits that may not be readily identified by existing screens (refer to Table 1 for a summary of SCREEN activities), such as the MoCA 8.1, MMSE, and Qmci. The SCREEN is a short version of the BrainFx 360 Performance Assessment, which is designed to assess cognitive, physical, and psychosocial areas of neurofunction [74]. This is a 90-minute test administered digitally to test 26 cognitive domains across 49 tasks that are timed, scored, and subsequently compared with the Living Brain Bank (LBB), a database of all BrainFx 360 and SCREEN tests collected to date. The 7 activities used on the SCREEN were taken directly from the BrainFx 360 on the basis of clustering and regression analyses of LBB records in 2016 (N=188) [75]. The reliability of the BrainFx 360 has been validated in healthy adults (mean 22.9 years of age, SD 2.4 years), and results suggest that the overall test-retest reliability of the tool is high (intraclass correlation coefficient=0.85 [74]); however, only 2 of the 7 cognitive domains selected for the SCREEN have reliability coefficients above 0.70 (visual-spatial and problem-solving abilities). To date, BrainFx 360 has been used in clinical settings to assess neurofunction among youth and in a variety of other rehabilitation settings.

**Table 1 table1:** Summary of SCREEN activities.

Activity	Description	Time to complete (s)
Abstract reasoning	Twenty everyday items are displayed, and the patient touches the item on the screen and slides each item, one at a time, into 1 of the 5 categories into which they best belong, while being timed.	90
Constructive ability	Two rounds of a photo being displayed and breaking into 9 pieces. The patient touches the pieces and slides each piece into a grid to reassemble, while being timed.	90
Prioritizing	Five everyday activities or tasks are presented, and the patient is told what time of day it is (eg, 7 PM), and the patient touches the screen and slides each item to prioritize the order in which the activities or tasks should be completed.	60

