At the end of each SCREEN, the patient will be prompted by the app to consent to contribute their scores to a database of results maintained by BrainFx, known as the LBB. The mean and SD of the LBB database will be updated in response to the addition of every new SCREEN. The patient’s performance on the SCREEN will be evaluated by comparing their results with the global reference population (ie, all available SCREEN results in the LBB at the time of testing). Filters are available that allow the HCP to compare the patients’ results with subcohorts using factors such as gender, education, age, or primary diagnosis. Individual SCREEN results reports display the individual’s activity score, the LBB mean (for the global reference population unless the operator selects subcohorts based on selected filters), and whether the activity score falls within 1 SD of the LBB mean. If the patient’s activity score falls 1 or more SD below the global mean, it is classified as an *area of challenge*. The HCP is instructed to use their clinical judgment to interpret the results by applying any number and combination of filters relevant to the patient. For the purpose of this study, the patient’s performance will be compared against all results in the LBB completed by people aged 55 years and older at the time of testing.

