To determine the sensitivity and specificity of the SCREEN in comparison with the Qmci, the results of both screens will be classified in binary format as healthy or not healthy, where *healthy* denotes SCREEN=no areas of challenge in all 7 activities and Qmci≥67 and *unhealthy* denotes SCREEN=1 or more areas of challenge and Qmci≤67. Consistent with consensus guidelines for screening for cognitive impairment [37,49,50], the research protocol will also require HCPs to refer patients to their primary care physician for further evaluation if they receive an abnormal score on the Qmci or significant concerns on the SCREEN. The SCREEN does not have a standardized cut-off score that can be used to classify results as abnormal. Therefore, in consultation with and on the recommendation of the SCREEN developers, for the purpose of the research protocol, a set of cut-off scores was developed to classify SCREEN results as normal (zero areas of challenge), some concerns (≤3 areas of challenge), or significant concerns (≥4 areas of challenge). All HCPs in this study will be OTs who are trained to assess individuals’ abilities or disabilities through the use of standardized testing and functional observation. As a result, the study protocol includes a condition that referral decisions for physician oversight or further testing are the purview of the HCP and their clinical judgment. This became the proxy gold standard for a positive screen in this research study.

Following the review of the results at each appointment, the HCP will provide patients with a handout that summarizes recommendations for supporting cognitive health. If the SCREEN identifies any *areas of challenge,* the patient will also receive a handout developed by BrainFx containing tailored strategies to strengthen brain health and manage deficits in those areas.

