#### Descriptive and Inferential Analysis

Descriptive data will be described using frequencies and percentiles and compared using the chi-square test or Fisher exact test as necessary. Continuous data will be analyzed for central tendency and variability; categorical data will be presented as proportions. Normality will be tested using the Shapiro-Wilk test, and nonparametric tests will be performed using the Mann-Whitney U test*.* Statistical significance will be considered at a *P* value of .05, with 90% CI provided where appropriate. We powered the exploratory analysis to validate the SCREEN using an estimated effect size of 12%, with the understanding that Canadian prevalence rates are not available [29], and determined that we needed at least 114 participants. For test-retest reliability, using 90% power and a 5% type 1 error rate, we will require a minimum of 58 test results.

MCI test outcome data will be coded into a binary format of *healthy* or *unhealthy* (where unhealthy indicates a positive result on the test, ie, 1 or more *areas of challenge* on the SCREEN results, or a score of ≤67/100 on the Qmci) to account for the difference in categorical versus continuous outcome variables. For this reason, sensitivity and specificity will be determined using cross-tabulation rather than using the area under the curve using receiver operating characteristic curves. A principal component analysis with varimax rotation will be used to better understand the derivation of components’ contribution to screen test outcomes and to explore the differences between a conventional MCI screen (Qmci) and one that is intended to be more ecologically valid by assessing functional impairment (SCREEN). Binary logistic regression will examine the effects of variables such as age, education, self-reported comfort with technology, anxiety before and after completing the MCI tests, and sleep levels on the results. The internal consistency of both the SCREEN and Qmci will be assessed using Cronbach α. Test-retest reliability, the ability of a measurement instrument to reproduce results on 2 or more occasions (ceteris paribus), will be assessed using an intraclass correlation coefficient [106].

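### SCREEN accuracy is planned at a single lenient cut-off (1 or more of 7 areas of challenge), and ROC analysis is rejected for a reason that is not valid

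*Protocol article*

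**What the plan says.** Under The SCREEN, an activity is an area of challenge if the "activity score falls 1 or more SD below the global mean". For this study the comparison group is narrowed: performance is "compared against all results in the LBB completed by people aged 55 years and older at the time of testing".

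Under Psychometric Evaluation, a healthy result "SCREEN=no areas of challenge in all 7 activities and Qmci≥67" is set against an unhealthy one, which "denotes SCREEN=1 or more areas of challenge and Qmci≤67". A Qmci of exactly 67 falls in both definitions there. Descriptive and Inferential Analysis counts it as positive, with "or a score of ≤67/100 on the Qmci" on the unhealthy side.

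That section gives the difference between categorical and continuous outcomes as the reason for the binary coding, and concludes that "sensitivity and specificity will be determined using cross-tabulation rather than using the area under the curve using receiver operating characteristic curves".

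Psychometric Evaluation also says that the SCREEN has no standardised cut-off. It grades the same count in three levels for the research protocol: normal at zero, "some concerns (≤3 areas of challenge), or significant concerns (≥4 areas of challenge". Significant concerns is a trigger for physician referral, subject to the provider's judgment. Any area of challenge leads to a tailored handout.

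**The concern.** There are two linked problems.

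First, the argument against ROC does not hold. The method does not require both tests to be the same type of variable. Qmci ≤67 is a binary reference, and the SCREEN count is ordered, as the three-level grading already assumes.

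Second, the one cut-off left in the analysis is lenient and unvalidated. Seven chances to fall 1 SD below a mean, with one enough to be positive, can flag many people who are typical of the reference group. The protocol gives neither an expected positive rate nor a justification of this cut-off for accuracy.

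The abstract's Conclusions say that the results will help the developers decide whether rigorous controlled testing is warranted. If specificity at 1 or more comes out low, the planned table cannot show whether the tool discriminates poorly or the rule is too loose. The category of 4 or more, which the protocol uses for referral, is never evaluated for accuracy.

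**Working it through.** The protocol states no expected SCREEN-positive rate or specificity, so there is no figure to reproduce.

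**Inputs from the protocol:** 7 activities; positive at 1 or more; threshold 1 SD below the LBB mean for age 55 and older; grading at 0, ≤3 and ≥4.

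**Assumptions (not in the protocol):** normal activity scores and a common inter-activity correlation ρ, shown over a range.

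**Step 1. Rate per activity.** p = Φ(−1) = 0.1587.

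**Step 2. Independent activities.** P(≥1 of 7) = 1 − (1 − 0.1587)^7 = 1 − 0.298 = 0.702.

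**Step 3. Correlated activities.** With a one-factor normal model, q(u) = Φ((−1 − √ρ·u)/√(1−ρ)). The binomial tail P(≥m of 7 | q(u)) is then averaged over u ~ N(0,1).

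| Areas of challenge | ρ = 0 | ρ = 0.3 | ρ = 0.5 | ρ = 0.7 |
|---|---|---|---|---|
| ≥1 | 70.2% | 56.2% | 47.5% | 38.6% |
| ≥2 | 30.8% | 29.7% | 27.8% | 25.3% |
| ≥3 | 8.5% | 14.8% | 16.8% | 17.8% |
| ≥4 | 1.5% | 6.7% | 9.9% | 12.6% |

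At ρ = 0.8 and 0.9 the first row falls to 33.6% and 27.7%. Such values fit poorly with the statement that "only 2 of the 7 cognitive domains selected for the SCREEN have reliability coefficients above 0.70". If two measures each have reliability of at most 0.70, their observed correlation cannot exceed about √(0.70 × 0.70) = 0.70. Those coefficients come from young adults, so this is a guide and not a bound for this population.

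**Step 4. Score shape.** If 12-14% of the reference group, instead of 15.9%, fall below the threshold on each activity, P(≥1) is 59-65% at ρ = 0, 47-52% at 0.3 and 39-44% at 0.5.

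**Step 5. Participants who differ from the LBB group.**
- Scoring 0.3 SD better moves the effective threshold to −1.3 SD (p = 0.097). P(≥1) is then 51%, 40%, 34% and 27% at ρ = 0, 0.3, 0.5 and 0.7.
- Suppose a share w of LBB records is impaired by d SD. The LBB mean is −wd and its SD is √(1 + w(1−w)d²), in units of the unimpaired group. For w = 0.2 and d = 1, the threshold is −0.200 − 1.077 = −1.277, and 52% to 28% of unimpaired people are flagged (ρ = 0 to 0.7). For w = 0.3 and d = 1.5, it is −0.450 − 1.213 = −1.663, and 29% to 15% are flagged.

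**Step 6. What the planned table would hide.** As an illustration, take ρ = 0.3 and impaired people 0.75 SD lower on every activity. The AUC of the 0-7 count is 0.76.

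| Cut-off | Sensitivity | Specificity |
|---|---|---|
| ≥1 | 0.88 | 0.44 |
| ≥2 | 0.71 | 0.70 |
| ≥3 | 0.53 | 0.85 |
| ≥4 | 0.35 | 0.93 |

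Only the first row would be reported.

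**The case against.** Cross-tabulation at a cut-off stated in advance is a legitimate way to obtain sensitivity and specificity. The study calls itself preliminary, and a lenient threshold suits a tool meant to miss few cases. All of that stands. The defect is that this is the only operating point, defended by a reason that does not exclude others.

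A reader might infer that the protocol evaluates a cut-off it never uses. The text does not support that. One or more areas of challenge triggers the handout and marks the boundary of the normal category. The 1-or-more and 4-or-more rules serve different purposes and do not contradict each other.

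A reader might also turn 39-70% flagged into an expected specificity of about 30-61%, fixed whatever the tool can do. That does not follow. Specificity will be calculated in Qmci-negative participants, not in people who resemble the LBB. The LBB is not described as a healthy norm: its filters include primary diagnosis, and the parent test has been used in rehabilitation settings. Study patients exclude several diagnoses linked to cognitive deficits. If impaired records lower the LBB mean and widen its SD, fewer unimpaired participants are flagged, as step 5 shows. LBB composition, correlation and score shape are not given.

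Finally, the abstract's Results say that data collection was halted and analysis is in progress, so pre-specification may no longer be possible. That affects how added analyses are labelled, not whether they are worth doing.

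**Conclusion.** The point holds in a limited form. The stated reason for rejecting ROC is wrong, and it leaves SCREEN accuracy known at one lenient, unvalidated cut-off.

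Under normal scores and ρ between 0.7 and 0, that cut-off flags about 39-70% of reference-type people, against about 13-1.5% at 4 or more. The direction is robust across the assumptions tried. The level is not: the step 5 scenarios bring it down to between 15% and 52%. None of these figures predicts the study's specificity.

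This should be fixed, but it does not invalidate the planned cross-tabulation. It limits what the study can tell the developers, and the remedy needs no new data.

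**What to change.** In Descriptive and Inferential Analysis:

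- Delete the sentence rejecting ROC.
- Keep the planned cross-tabulation at 1 or more areas of challenge.
- Add an ROC curve with AUC and confidence interval for the 0-7 count against Qmci ≤67.
- Report sensitivity and specificity with confidence intervals at every count, including 4 or more.
- Treat any mean of the activity scores as exploratory, since the SCREEN as described has no total score.
- Label the additions post hoc unless they were fixed before results were seen, and do not present a cut-off chosen from these data as validated.
- State that the figures measure agreement with Qmci. Reconcile this with Psychometric Evaluation, which names the provider's referral judgment as the proxy gold standard.

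This concerns reporting of accuracy only and implies no change to the referral rule.

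The cost is revised wording and a few lines of analysis on SCREEN and Qmci results that the study collects anyway. The downside is that several operating points are reported instead of one.

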#### Psychometric Evaluation

Data collection for the psychometric evaluation study will take place in person at the patients’ respective FHT. Standard operating procedures have been developed for the research study, which will be followed by the research team and HCP staff trained in the study protocol and administration of all data collection tools. A member of the research team will observe at least one in-clinic HCP data collection visit to confirm adherence to the protocol and training procedures.

To assess the reliability and perceived usefulness of the SCREEN, depending upon when a patient enters the study, they may repeat the screening protocol up to 4 times. Each visit is structured around the administration of 2 MCI screens; the *GAS-10* [81,82]; and a series of questions that measure the patient’s use of technology, change in their general health and well-being, or any interactions with the health care system related to MCI that occur in the 3 months since their last appointment. The HCP will be required to complete a patient encounter form at each appointment, which includes a summary of the patient’s MCI screen results, any referrals, and their responses to these questions.

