The patients’ first appointment will take approximately 45-60 minutes (to account for onboarding), and all subsequent appointments (up to 4 screening test pairs, depending on the patient’s study entry date) will take approximately 45 minutes to complete. Rolling recruitment of patients will occur over an 18-month period and will end when a minimum of 2 and a maximum of 4 SCREEN-Qmci test pairs are completed every 12 weeks. In older adults, with no diagnosis of MCI or dementia, measures of cognitive abilities, including verbal fluency, attention, and intelligence [100], and measures of executive functioning [101] remain stable for anywhere from 4 to 8 weeks or from 1 to 5 years between test and retest (controlling for the effects of normal aging [100]). To date, there are no clear guidelines on the optimal time between tests [102,103]. Streiner [104] recommends longer periods to avoid recall bias. Furthermore, greater practice effects are experienced with shorter test-retest intervals [62]. The 3-month interval was therefore selected to minimize such confounds and is justified given the stability of the constructs under investigation. A randomization process will determine the order of screen administration at each visit. The Qmci will be administered using a pen and paper. HCPs will be provided with identical tablets, preloaded with the SCREEN app software.

The GAS-10 will be administered just before and immediately after the administration of the first MCI screen (eg, the SCREEN) and immediately followed by the administration of the second MCI screen (eg, the Qmci) at each appointment. After completing the 2 MCI screens, the HCP will manually calculate the results for the Qmci, log in to the BrainFx portal to retrieve the SCREEN report, and review both sets of results with the patient. The Qmci cut-off score for distinguishing MCI from normal cognition is ≤67/100 [88]. The SCREEN does not include scoring guidelines for a cut-off score but identifies whether a score on any of the 7 tasks is an *area of challenge*.

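### The covariate regression uses a second GAS-10 reading that follows one screen and precedes the other, and puts six named terms on a dichotomised result in 114 patients

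*Protocol article*

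**What the plan says.** Under Descriptive and Inferential Analysis, the Protocol article codes each screen as healthy or unhealthy: one or more areas of challenge on the SCREEN, or 67 or less on the Qmci. A binary logistic regression is then to examine the effects of age, education, self-reported comfort with technology, "anxiety before and after completing the MCI tests, and sleep levels on the results". The list is introduced as examples. The text does not say which screen's result is the outcome.

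The same section gives the sample size: "determined that we needed at least 114 participants", obtained "using an estimated effect size of 12%, with the understanding that Canadian prevalence rates are not available".

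Under Psychometric Evaluation, the GAS-10 is "administered just before and immediately after the administration of the first MCI screen", and the second screen follows directly. On order, "A randomization process will determine the order of screen administration at each visit". Results are calculated and discussed with the patient only once both screens are done.

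The section on the 10-Item GAS gives two purposes for the paired measure: to control for anxiety when performance is interpreted, and to explore changes in performance or anxiety linked to the tablet.

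**The concern.** A covariate offered as an explanation of a test result should precede that result. For whichever screen comes first, the second GAS-10 does not: a patient who finds the test hard may leave it more anxious. Putting that reading beside the pre-test one conditions on a possible effect of the outcome, and this can bias the pre-test coefficient that the GAS-10 was included to estimate. For the second screen, the same reading is a proper pre-test value, and no later reading is described.

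Separately, a logistic model is limited by the size of its smaller outcome class. With few positives and six or more terms, odds ratios are unstable and tend to be exaggerated, and real effects are easily missed. The Qmci total (0 to 100) and the SCREEN activity scores are collected anyway, so the information lost by dichotomising is available.

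This matters because Limitations says that the analysis will account for self-selection by comfort with tablets, and this regression is the only model named that includes that variable.

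**Working it through.** **1. Timing.** The sequence in Psychometric Evaluation is GAS-10 (first), screen A, GAS-10 (second), screen B, where A and B are SCREEN and Qmci in random order.
- Outcome is screen A: the first reading is before it and the second is after it.
- Outcome is screen B: both readings are before it and none is after it.

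So for the Qmci result, the second reading is post-test in visits where the Qmci came first and pre-test in the others. The same holds for the SCREEN. The regression wording, anxiety after completing the tests, fits neither case for both screens.

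**2. Effect on the pre-test coefficient (illustration, all coefficients assumed).** Let P be pre-test anxiety, Y = bP + e the score (variance of e = 1), and A = aP - cY + u the anxiety after that screen (SD of u = t). With A in the model, the coefficient on P becomes b + [c/(c² + t²)](a - cb). Take b = -0.30 and a = 0.8.
- c = 0.1, t = 1: -0.30 + (0.1/1.01)(0.83) = -0.22
- c = 0.3, t = 1: -0.30 + (0.3/1.09)(0.89) = -0.06
- c = 0.3, t = 0.5: -0.30 + (0.3/0.34)(0.89) = +0.49

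With c = 0 there is no bias. The size depends on c and t, which the article does not give.

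**3. The figure of 114.** No test, power or precision is stated for it, so it cannot be reproduced uniquely. Reading 12% as a proportion, with a 90% interval (the article says: "Statistical significance will be considered at a *P* value of .05, with 90% CI provided where appropriate") and an assumed half-width of 5 points, gives 1.645² × 0.12 × 0.88 / 0.05² = 114.3. This fits a prevalence reading but does not prove it. A 95% interval of ±6 points gives 113, and a one-sample test of 0.75 against 0.87 (two-sided, 90% power) gives 114.

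**4. Events per term, Qmci outcome.** The named terms are age, education, technology comfort, anxiety before, anxiety after and sleep: six. Events = 114 × positive rate.
- 10% (assumed): 11.4 events, 1.9 per term
- 12%: 13.7 events, 2.3 per term
- 20% (assumed): 22.8 events, 3.8 per term
- 30% (assumed): 34.2 events, 5.7 per term
- 42% (upper MCI prevalence quoted under MCI Disorder): 47.9 events, 8.0 per term

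At 12%, ten events per term would need 6 × 10 / 0.12 = 500 patients, and five would need 250. Five and ten are conventional yardsticks; the article sets none.

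**5. Events per term, SCREEN outcome.** Assume normal activity scores and a sample like the reference group, with a cut 1 SD below the mean on any of seven activities. If the activities are independent, the positive share is 1 - (1 - 0.159)⁷ = 70%, which leaves 34 negatives, or 5.7 per term. With assumed correlations of 0.2, 0.4, 0.6 and 0.8, the smaller class is 45, 55, 49 and 38, or 7.5, 9.2, 8.2 and 6.4 per term.

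**6. Cost of dichotomising.** This was simulated with 114 patients, six predictors (two correlated 0.8), a normal score and an assumed effect of 0.3 SD. Power for the logistic model is about 45% at 12% positive, 56% at 20% and 67% at 42%. Linear regression on the continuous score has about 83% to 88% throughout.

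**The case against.** The best defence is that this is a secondary covariate analysis in a preliminary, exploratory study, reported in a condensed article. The article does not say that all six variables enter one model. It calls 12% an effect size and states no Qmci-positive rate, and Limitations expects people worried about their cognition to volunteer, which would raise the rate. For the SCREEN, the smaller class is larger. The simulation assumes a normal, linear score, which favours linear regression. All of this stands. It is why the sparse-event point is given as a range, and why 14 positives must not be read as a stated figure. It does not remove the point, because the events per term stay below ten in every case examined.

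Four stronger readings are tempting and are not supported.
- A reader might infer that screen order is left out of the model. The covariate list is open, and the analysis plan is not shown, so this is silence and not exclusion.
- A reader might infer, because "they may repeat the screening protocol up to 4 times", that visits are pooled as if independent. The article does not say so. The only use of repeat testing that its analysis section states is test-retest reliability.
- A reader might take "nonparametric tests will be performed using the Mann-Whitney U test", or the chi-square test, as misapplied to paired data. Neither is assigned to a within-patient comparison.
- A reader might say that the second GAS-10 captures the reaction to the result. Results are reviewed only after both screens, so it can reflect the experience of taking the first screen but not of hearing its outcome.

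The GAS-10 section also already foresees exploring variation in anxiety, so treating change in anxiety as an outcome agrees with a stated purpose.

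**Conclusion.** The point holds in two parts. The firmer one rests on the text alone: the regression section and the procedures section disagree on when anxiety is measured. With order randomised, a single coefficient for the after reading mixes a possible consequence of one screen with a baseline for the other. Its bias on the pre-test effect could be modest or could reverse the sign; only the mechanism is certain.

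The second part is that six or more terms on a binary result are too many for 114 patients. The ratio is 2.3 events per term if 12% is the Qmci-positive rate, 1.9 to 8.0 over 10% to 42%, and about 5.7 to 9.2 for the SCREEN under assumed correlations. Data collection was interrupted in March 2020, so if fewer than 114 patients were tested, the ratios at any given rate are lower.

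The sensitivity and specificity cross-tabulation is not affected. The regression should be corrected before its results are interpreted.

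**What to change.** - Reconcile Psychometric Evaluation with Descriptive and Inferential Analysis, so that both state the same GAS-10 time points.
- For each screen, adjust only for the GAS-10 taken immediately before it: the first reading for the screen given first, the second reading for the screen given second.
- Treat change in GAS-10 across the first screen as an outcome, not as a predictor of that screen.
- Make linear regression of the continuous Qmci total on the covariates the main covariate analysis, with the SCREEN activity scores as exploratory. Keep the binary coding for the cross-tabulation.

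This needs only plan wording; the data and software are unchanged. The costs are that effects are in score points and not odds ratios, so the question moves from what predicts a positive screen to what predicts the score. The SCREEN also needs seven models, one per activity, because no continuous total is described. Those should be labelled exploratory because of the multiple testing.
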